#### Sample size {14}

Our sample will consist of 990 children aged 4 to 5 years old, distributed in groups of > 15 per kindergarten. Our sample size calculation considered the following input parameters: (1) two groups in a cluster design with an allocation ratio of 1:1; (2) a minimal detectable effect size difference of *d* = 0.27, which is the upper limit confidence interval for the effect size reported on SEL skills derived from 114 studies [1], with a mean of 0.219 (95% CI = 0.171–0.267). In this meta-analysis, the most common measure used to track SEL was the *Strength and Difficulties Questionnaire* [27], which is our primary outcome measure and rated by teachers and parents. Such a difference of 0.27 is described as a small effect size, according to the traditional benchmarks proposed by Cohen [33]. When considering only the effect sizes among the youngest (called by Cipriano et al. [1]) as elementary schools (Kindergarten [5 years old] to 5th grade [10 years old]) from exclusively randomized controlled trials and using SEL skills as outcomes, the average adjusted effect size at post-assessment was 0.241 (derived from 96 effect sizes). Therefore, our minimum expected effect size is closer to the state-of-the-art. However, the effect sizes depend on the population, outcome, and nature of the implemented intervention. Researchers have recently used data from systematic reviews and meta-analyses to recalculate the cutoffs for the difference [34–36]. (3) Intraclass coefficient correlation-derived SDQ domains ranged from 0.015 to 0.064 [37]; (4) Power was 0.8, and the adopted significance level was 0.05.

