A parallel, two-group cluster-randomized design will be used to test whether the Nor-SSEL (active intervention) mean is different from the Group “play” (active control) mean. The comparison will be made via a two-sided *t*-test with degrees of freedom based on the total number of subjects [38, 39], with a Type I error rate (*α*) of 0.05. The common subject-to-subject standard deviation for both groups is assumed to be 1, the intracluster correlation coefficient is considered to be 0.065, and the coefficient of variation of cluster sizes is assumed to be 0.65. For a power of 80%, with 30 kindergartens of 15 subjects per kindergarten in Group *Nor-SSEL* (totaling 450 children) and 30 kindergartens of 15 children per kindergarten in Group *Play* (totaling 450 subjects), the detectable mean difference (μ1 − μ2) is 0.27. Therefore, 900 children in 60 kindergartens are needed. To compensate for the potential decrease in power due to attrition, we will recruit 990 children from 66 kindergartens. The detectable difference was computed using PASS version 23.0.1.

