#### Statistical methods

### Statistical methods for primary and secondary outcomes {20a}

Due to the longitudinal (measured by three repeated raw continuous scores) and multilevel design (children nested in schools), two multilevel mixed-effects models will assess the intervention’s effectiveness on primary and secondary outcomes. We will use the maximum-likelihood estimator and, therefore, invoke the full-information maximum likelihood method to address missing data, assuming a missing mechanism of missing at random. The residuals will be a priori specified with a first-order autoregressive structure to account for within-subject correlation across time points (three repeated time points).

For all outcomes, an unstructured covariance matrix will be used to estimate the covariance between the random intercept (baseline assessment of the outcome) and random slope for time (i.e., potential speed of the improvement on the outcomes) at the children-level, allowing for maximal flexibility in modeling their relationship without imposing symmetry or independence.

Depending on the distribution of the outcomes, non-linear models can be implemented; however, we do not have a specific a priori model for this approach, as it is necessary to evaluate the distributional features of the observed data.

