Finally, we examine the interplay between the SDQ and EmQue scores using the latent change score approach [51] to understand whether empathy influences SEL skills (or vice versa). The adopted statistical significance level will be 0.05, and all analyses will be conducted using Mplus version 8.11 [52].

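### Maximum likelihood with 60 to 66 randomised kindergartens makes a kindergarten-level test of the arm effect slightly liberal, at about 6% instead of 5%

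*Protocol article*

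**What the plan says.** Under Statistical methods for primary and secondary outcomes {20a}, two multilevel mixed models, one for the primary and one for the secondary outcome, use three repeated scores with children nested in schools. On estimation: "We will use the maximum-likelihood estimator and, therefore, invoke the full-information maximum likelihood method". Missing data are assumed missing at random. The residuals are first-order autoregressive, and a random intercept and a random slope for time are described at child level. No kindergarten-level random term, primary contrast or reference distribution is written out.

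Under Methods for additional analyses {20b}: "The adopted statistical significance level will be 0.05", and "all analyses will be conducted using Mplus version 8.11".

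Under Sequence generation {16a}, randomisation is by kindergarten. Under Sample size {14}, "900 children in 60 kindergartens are needed", and 66 kindergartens with 990 children are recruited to allow for attrition. The only degrees-of-freedom rule in the article is also there, for the power calculation: a "two-sided *t*-test with degrees of freedom based on the total number of subjects".

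**The concern.** In a cluster-randomised trial the arm effect is a contrast between kindergartens. Its precision is judged from K kindergartens, with about K − 2 degrees of freedom (58 or 64 here), not from 900 or 990 children. Two features then push the test in the same direction:

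- Maximum likelihood estimates the between-kindergarten variance without allowing for the two estimated arm means. In the balanced case the variance is too small by the factor (K − 2)/K.
- A normal reference, or a t reference with degrees of freedom counted in children, uses a critical value of about 1.96, where t on K − 2 degrees of freedom needs about 2.00.

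Both remain even when the kindergarten is correctly in the model. At stake is the stated error rate of the primary and secondary tests and the coverage of their confidence intervals.

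**Working it through.** **Inputs from Sample size {14}.** Two-sided level 0.05 and power 0.80 ("Power was 0.8, and the adopted significance level was 0.05"); "a minimal detectable effect size difference of *d* = 0.27"; standard deviation 1; intracluster correlation (ICC) 0.065; coefficient of variation (CV) of cluster size 0.65; 15 children per kindergarten; K = 60 needed, 66 recruited.

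**Step 1. Reproduce the plan's own figure.**
- L = 15 / (15 + 0.935/0.065) = 0.5105.
- Relative efficiency = 1 − 0.65² × L × (1 − L) = 0.894.
- Design effect = (1 + 14 × 0.065) / 0.894 = 1.91 / 0.894 = 2.136.
- Standard error = √(2 × 2.136 / 450) = 0.0974.
- Detectable difference at 80% power with 898 degrees of freedom = 0.273, which rounds to the stated 0.27. Power at 0.27 is 79.1%.

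The inputs are therefore read as the plan meant them.

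**Step 2. Size of a kindergarten-level test, equal clusters.** True size = P(|t on K − 2 df| > c × √((K − 2)/K)), where c is the critical value used. With c = 1.96:
- K = 60: 1.96 × √(58/60) = 1.927, and 2 × P(t₅₈ > 1.927) = 5.89%.
- K = 66: 1.96 × √(64/66) = 1.930, and 2 × P(t₆₄ > 1.930) = 5.80%.

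The contributions of the two features:

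| Variance and reference | K = 60 | K = 66 |
|---|---|---|
| ML, normal | 5.89% | 5.80% |
| ML, t on number of children − 2 | 5.85% | 5.77% |
| Unbiased variance, normal | 5.48% | 5.44% |
| ML, t on K − 2 | 5.38% | 5.35% |
| Unbiased variance, t on K − 2 | 5.00% | 5.00% |

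Coverage of a nominal 95% interval in the first row is 94.1% and 94.2%.

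**Step 3. The plan's unequal clusters.** Two-level data with one score per child were simulated under no effect, 8,000 runs per setting, with Monte Carlo standard error about 0.25 points. At ICC 0.065 and CV 0.65:

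| Method | K = 60 | K = 66 |
|---|---|---|
| ML, normal | 6.1% | 6.2% |
| REML, normal | 5.7% | 5.6% |
| REML, t on K − 2 | 5.3% | 5.2% |

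Over all settings tried (ICC 0.015, 0.065 and 0.15; CV 0 and 0.65), ML with the normal reference ran from 5.3% to 6.3%. The gap between 6.1–6.2% and the equal-cluster 5.8–5.9% is at most about 1.4 Monte Carlo standard errors, so it should not be read as a firm extra effect of unequal sizes.

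**Step 4. Which p-values change.** In the equal-cluster case, a correct test at 5% needs an ML ratio of 2.002 / 0.983 = 2.036 (K = 60) or 1.998 / 0.985 = 2.029 (K = 66). On the normal scale these are p = 0.042 and 0.043. Only reported p-values between about 0.042 and 0.05 would change sides.

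**Step 5. Dependence on the model actually fitted.**
- If arm-by-time is tested against child-level error and kindergartens do not differ in change, the same formula with 898 or 988 degrees of freedom gives about 5.1%.
- If kindergartens do differ in change and the model leaves this out, size = 2 × P(Z > 1.96 / √(1 + 14 × ICC of change)). An assumed ICC of change of 0.015 gives 7.5%, and 0.065 gives 15.6%.

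**The case against.** The strongest reply is that the article does not fix the test to which these figures apply. It plans three repeated scores and describes random terms only at child level. The 5.8–5.9% belongs to a balanced comparison of kindergarten means, and Step 5 shows that other readings give other numbers. This stands, and it is why the point is conditional.

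A reader might infer that the primary test will run at 5.8–5.9%. The article does not support that, because contrast and kindergarten-level terms are open. A reader might also infer that the kindergarten is left out of the model, with error rates up to 15.6%. That is not supported either: the article calls the design multilevel with children nested in schools, and not listing a kindergarten term is not the same as excluding it.

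Second, no normal reference is stated; it is inferred from the choice of ML in Mplus. This also stands, but little depends on it. The child-based degrees of freedom in the sample-size section give almost the same size, and ML alone exceeds 5% even with the right t reference.

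Third, a small-sample correction may sit in an analysis plan not shown here. Its absence is therefore not the complaint. The complaint is about the estimator and software that the article does fix.

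Fourth, ML could be defended as needed for missing data. That does not hold. The incomplete variable is the repeated outcome, and REML uses the same observed scores under the same missing-at-random assumption.

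Finally, 60 kindergartens need not be the number left at the end. The article does not say that kindergartens, rather than children, will be lost. The results for 60 and 66 are close enough that this does not matter.

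**Conclusion.** The point holds in conditional form and is minor. If the arm or arm-by-time effect is tested against between-kindergarten variance, as cluster randomisation requires, the stated estimator with a normal or child-based reference gives a size of roughly 5.8–5.9% with equal clusters and 6.1–6.2% at the plan's ICC and cluster-size variation. The excess is about one percentage point, and a result with p clearly below 0.04 is not affected. These figures rest on a two-level model with one score per child and with the kindergarten correctly included. They do not give the size of a model that the article has not fully specified. Choosing ML with this many clusters is not a serious error; a better choice is available at little cost.

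**What to change.** Amend the estimation sentence for the SDQ and EmQue models along these lines: the models will be fitted by restricted maximum likelihood in a mixed-model package, with random effects for kindergarten (including variation between kindergartens in change over time), and the arm effect will be tested with Kenward-Roger or Satterthwaite degrees of freedom. State the contrast that forms the primary test in the same place. Limit the Mplus statement to the latent-variable models.

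Multiplying the ML standard error by √(K/(K − 2)) inside Mplus is not a general substitute. It is exact only for a balanced comparison of kindergarten means, and it would overcorrect a contrast driven by child-level variance.

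The cost is a second package for two models and slightly lower nominal power. With the plan's inputs and a difference of 0.27, moving from child-based to K − 2 degrees of freedom takes power from 79.1% to 77.8% at 60 kindergartens and from 82.7% to 81.7% at 66. The change is best fixed before outcome data exist, since a correction chosen after a borderline p-value would be open to challenge.

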#### Moderators and mediators

The moderator will be the parents’ socioeconomic status (SES). Parents will self-report the same items as in [19], namely the education levels (years of schooling) and the household incomes. SES plays an important role in shaping children’s socio-emotional trajectories, and children from lower SES backgrounds are found to face increased difficulties throughout school compared to their peers [30]. Given the disparities between children from different socioeconomic statuses (SES), it may moderate the effectiveness of socio-emotional learning (SEL) interventions. By including SES as a moderator in this randomized controlled trial, we will be able to examine whether the program has an impact across social strata, ensuring that the findings are not only generalizable but also sensitive to issues related to SES.

The mediator is a continuous joint attention score, considered a predictor of subsequent functioning in the social, communicative, and cognitive domains [31], where the kindergarten teachers will be trained [32]. The Joint Attention Scale consists of six naturalistic examiner-initiated prompts designed to elicit a response to joint attention. The available protocol for joint attention will be translated and adapted for use in Norway. As a mediator, its role in the modeling will allow us to explore how (mechanism hypothesis) the effects of the intervention might impact the outcomes.

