**INTERVENTIONS:**						
**Intervention:** **Second Step Early Learning (NOR ed.)**						
**Control condition: Free play**						
**ASSESSMENTS:**						
**SDQ** **(primary outcome)**			X		X	X
**EmQue** **(secondary outcome**			X		X	X
**Joint Attention Scale (mediator)**				X		
**Caregiver SES (moderator)**			X			
**Std. 1st grade screening test**						X

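### As described, the primary model uses parental SES only as a moderator; adding SES and SES-by-time terms would be a cheap, minor improvement in precision and in the credibility of missing at random

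*Protocol article*

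**What the plan says.** The section on statistical methods for primary and secondary outcomes {20a} specifies two multilevel mixed models on three repeated scores. It fixes a first-order autoregressive residual and a child-level random intercept and slope with unstructured covariance. The models "invoke the full-information maximum likelihood method to address missing data, assuming a missing mechanism of missing at random". No covariate or auxiliary variable is listed.

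The section on moderators and mediators makes parental SES (years of schooling and household income, self-reported) the moderator. Its reason is that "children from lower SES backgrounds are found to face increased difficulties throughout school compared to their peers". The participant timeline carries the same label, "Caregiver SES (moderator", with a single collection at t1. The consent section {26b} makes collection of SES depend on parental consent.

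The section on non-adherence and missing data {20c} adds multiple imputation under missing at random and a selection model under missing not at random. Neither names its variables. The discussion names attrition at the move from kindergarten to school as a risk.

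**The concern.** A likelihood analysis under missing at random is protected only against dropout that is explained by what is in the model. The plan singles out SES as a driver of later difficulties, and therefore of change as well as baseline level, over the period when it expects to lose children. Informants are not blinded, so response could differ by arm. If low-SES families leave one arm more than the other, a model without SES attributes part of the resulting shift to the intervention. SES also differs between kindergartens, and with 15 children per kindergarten the between-kindergarten variance limits precision. The value is already due to be collected at t1, so not using it in the primary model forgoes something for nothing.

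**Working it through.** **1. The plan's own figure.** Inputs from the sample size section {14}: "Power was 0.8, and the adopted significance level was 0.05"; "two groups in a cluster design with an allocation ratio of 1:1"; "The comparison will be made via a two-sided" t-test with "degrees of freedom based on the total number of subjects"; "The common subject-to-subject standard deviation for both groups is assumed to be 1"; ICC 0.065; coefficient of variation of cluster size 0.65; 30 kindergartens of 15 per arm.

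- L = 15 × 0.065 / (15 × 0.065 + 0.935) = 0.975/1.91 = 0.510.
- Design effect = (1 + 14 × 0.065) / (1 − 0.65² × 0.510 × 0.490) = 1.91/0.894 = 2.136.
- SE = √(2 × 2.136/450) = 0.0974.
- Detectable difference = (1.960 + 0.842) × 0.0974 = 0.273, against the stated 0.27. Power at exactly 0.27 is about 79%.

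The figure reproduces. It takes no credit for covariates, so leaving SES out costs nothing against it.

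**2. Precision forgone.** The documents give no SES-SDQ correlation, so these inputs are assumptions.

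- *Child level.* Take an SES-SDQ correlation s of 0.1-0.3 and a baseline-to-post correlation r of 0.5-0.7. With baseline in the model, the share of remaining variance removed by SES is 1 − (1 − R²)/(1 − r²), where R² = (r² + s² − 2rs²)/(1 − s²). For s = 0.2, r = 0.6: R² = 0.352/0.96 = 0.3667 and the share is 1 − 0.6333/0.64 = 1.0%. Over the grid it is 0.2-3.3%, which lifts 80% power to 80.1-81.3%.
- *Kindergarten level.* With equal clusters, the between-kindergarten part of the variance of the arm difference is 0.065/(0.065 + 0.935/15) = 51%. If SES removes 10-40% of that part and 2-4% of the rest, the variance falls by 0.51 × 0.10 + 0.49 × 0.02 = 6% to 0.51 × 0.40 + 0.49 × 0.04 = 22%, and power is 82-89%. That ignores baseline SDQ. If the further fall after baseline is 4-12%, power is Φ(2.802/√0.96 − 1.960) = 81.6% to Φ(2.802/√0.88 − 1.960) = 84.8%.

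Together: roughly 80-85% instead of 80%.

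**3. Bias.** Attrition implied by the plan: 1 − 900/990 = 9.1%. SES-related dropout by arm is assumed.

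- *Simulation* of 1,000,000 children per scenario, post score on arm and baseline, r = 0.6, s = 0.1-0.3. Dropout odds ratios are per SD lower SES, one per arm. The table gives the difference between the estimates without and with SES.

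| Dropout | 2 vs 2 | 2 vs 1 | 2 vs 0.5 |
|---|---|---|---|
| 9.1% | about 0 | 0.002-0.008 SD | 0.005-0.015 SD |
| 30% | about 0 | 0.008-0.023 SD | 0.015-0.046 SD |

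- *Bound* at 9.1%, if every loss in one arm is the lowest-SES child and losses in the other are random: the mean SES shift is φ(z)/(1 − 0.091) = 0.18 SD. Multiplied by the partial coefficient s(1 − r)/(1 − s²) = 0.040-0.132, this gives 0.007-0.024 SD.
- *Heavier dropout:* 25-35% in control (SES-related), 15-20% in Nor-SSEL (unrelated), SES effect on change 0.10-0.20 SD per SD. Bias is 0.02-0.08 SD.
- *Three waves,* dropout only between T2 and T3, half the SES effect present by T2. Using the observed T2 score, as the planned likelihood does, cuts the worst case from 0.070 to 0.052 SD. At average dropout near 9% the bias is 0.002-0.02 SD.

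**4. Which SES term.** In a three-wave likelihood, a time-constant SES term removed only about 30-55% of the T3 bias. SES-by-time terms removed essentially all of it. The reason is that a single coefficient averages the SES effect over the waves, while the bias comes from the part that grows between them.

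**The case against.** The strongest objection is that silence is not exclusion. The methods section gives no covariate list at all, and a journal article commonly leaves covariates, auxiliary variables and imputation variables to an analysis plan that is not shown here. That stands, and it is why this is a recommendation and not an error. What remains is that the article does fix the estimator, the missing-data assumption and the covariance structure, and gives SES a different, single role.

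Three stronger readings are tempting, and the documents do not support them.

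- A reader might infer that the trial loses power. The stated 80% assumes no covariates, and the baseline score already carries much of what SES would explain.
- A reader might infer that SES is available for every child. It is self-reported and depends on consent, so the covariate will have missing values of its own, and a residual bias of exactly zero is an ideal.
- A reader might infer that the planned analysis is biased. That needs SES-related dropout that differs by arm, and nothing in the documents shows such a pattern.

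It is also fair that the plan does not rest on the likelihood model alone. The selection model is meant for dropout that depends on things outside the model. But neither it nor the imputation is said to use SES.

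**Conclusion.** The point holds as a minor improvement. The unadjusted comparison is valid and the stated power stands. Giving SES no role in the primary model forgoes up to about 5 points of power, on assumed variance shares. It also leaves a small, conditional bias: about 0.00-0.02 SD at the plan's implied 9.1% attrition, at most about 7% of the 0.27 SD target (0.02/0.27). At an assumed control dropout of 25-35% it reaches about 0.05-0.08 SD, or 19-30% of the target. With equal SES-related dropout in both arms it is near zero. The SES-outcome correlations, variance shares and dropout gradients are all assumptions, since the documents give none. Only the ICC, cluster sizes, target difference and implied attrition come from the plan.

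**What to change.** In {20a}, pre-specify years of parental schooling and household income as covariates in both models, each with its interaction with time, because a time-constant term alone leaves much of the bias. State that missing SES values are modelled within the likelihood, so that children without them are kept. In {20c}, name the same variables for the multiple imputation. Keep the SES-by-arm moderator analysis separate. If the analysis plan already says this, a cross-reference is enough.

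The cost is a sentence in each section and a few more parameters, with no new data collection. The downside is that some parents will not report income, so that covariate needs its own missing-data assumption. The protocol version reviewed says recruitment has not begun, so the choice can be made now without any suspicion that the data drove it.

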### Interim analyses {21b}

N/A: No interim analyses are planned for this study.

### Methods for additional analyses (e.g., subgroup analyses) {20b}

We plan to test two mediation hypotheses: (a) random assignment will impact the joint attention score (continuous score), which in turn will impact the SDQ general score; (b) long-term distal and serial effects where random assignment will impact the joint attention score (continuous score), which in turn will impact the SDQ general score, which, lately, will impact the math and reading scores at the end of the first grade. Mediation analysis will be conducted under the counterfactual framework, where the models offer flexibility in estimation due to the exposure–mediator interaction [45], allowing the effects to be decomposed as described by VanderWeele [46].

We also plan to study the effectiveness of the intervention on the SDQ and EmQue subscales via a latent approach, where the CT-C(M-1) model [47] will be employed to disentangle methods (at least one of the parents and teachers) and trait effects (five domains of the SDQ and three domains of the EmQue) in the post-intervention assessment. We plan to run two different types of models: one considering the 50 polytomous items in total for the SDQ (i.e., 25 from teachers + 25 from parents for the SDQ) and 38 items for EmQue (19 teacher + 19 parent items for EmQue), given our robust sample size to use diagonally weighted least squares (WLSMV) as an estimator (the default estimator for ordinal observed variables). The other modeling approach is to create five parcels, one per SDQ domain, in the case of EmQue, or three parcels, as suggested by Eid et al. [47], which generates a more parsimonious model [7]. Therefore, given that our “items” are now five (SDQ) or three (EmQue) approximations of continuous outcomes, for the CT-C(M-1) model, we will use maximum likelihood with a robust standard error estimator. Within each domain, the balancing approach was used to create parcels (see “single factor analysis” parceling, Landis et al. [48]), where the item with the highest item-scale correlation is paired with the item that has the lowest item-scale correlation. The advantages and disadvantages of parceling have been discussed in several contributions [49, 50].

Finally, we examine the interplay between the SDQ and EmQue scores using the latent change score approach [51] to understand whether empathy influences SEL skills (or vice versa). The adopted statistical significance level will be 0.05, and all analyses will be conducted using Mplus version 8.11 [52].

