### Outcomes {12}

The primary outcome is child psychosocial adjustment measured using the *Strength and Difficulties Questionnaire* (SDQ; [27]), which will be answered by at least one of the parents and kindergarten teachers at baseline (T1), immediately after the 28 weeks of intervention (T2), and then 6 months after (T3) the transition to school (K1). The SDQ comprises 25 items and assesses five dimensions: emotional symptoms, conduct problems, hyperactivity/inattention, peer relationship problems, and prosocial behavior, which are the most common outcomes of SEL [1]. We will use the general continuous score for the analysis.

The secondary outcome is empathy, which at least one of the parents and teachers measures via the Empathy Questionnaire for Children (EmQue) toddler version. The questionnaire comprises 19 items assessing emotional contagion, attention to others’ feelings, and prosocial actions [28]. The tests are composed of two domains: cognitive and affective empathy. We will use EmQue’s general raw continuous score.

The exploratory distal outcome will measure the academic achievement score (last month of the first grade) in reading and math, represented by the standardized assessment tests (in Norwegian called *Kartleggingsprøver*) developed by the Norwegian Directorate for Education and Training [29]. The results of the tests are continuous scores for both reading and mathematics.

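### The subscale effectiveness model uses one post-intervention wave and names no baseline term, giving up precision that the baseline data could supply at almost no cost

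*Protocol article*

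**What the plan says.** The Protocol article treats the two questionnaires in two ways.

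- **Total scores.** Under Outcomes {12} the SDQ enters as one overall score ("We will use the general continuous score for the analysis"), and the EmQue likewise. Section {20a} analyses these with mixed models of outcomes "measured by three repeated raw continuous scores". The child-level terms are a "random intercept (baseline assessment of the outcome) and random slope for time", so the baseline is part of the model.
- **Subscales.** Section {20b} states an effectiveness aim: "We also plan to study the effectiveness of the intervention on the SDQ and EmQue subscales via a latent approach". The model is to separate rater effects from "trait effects (five domains of the SDQ and three domains of the EmQue) in the post-intervention assessment". For the SDQ, the item-level version is described as "one considering the 50 polytomous items in total for the SDQ (i.e., 25 from teachers + 25 from parents for the SDQ". The count for the other questionnaire is built the same way, from one set per rater: "38 items for EmQue (19 teacher + 19 parent items for EmQue". The second version forms parcels within the domains. No T1 item, T1 factor or T1 covariate is mentioned for either version.

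The T1 data exist. Sections {12} and {18a} have parents and teachers complete the SDQ and EmQue at baseline. Sections {16b} and {16c} release a kindergarten's allocation only after the baseline data of 15 children are in the system.

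**The concern.** The subscale analysis is presented as an estimate of effectiveness, not only as a measurement model, and the text fixes its wave, its indicators and its estimators. An analyst who followed it as written would compare arms at T2 with nothing carried over from T1.

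Only 60 to 66 kindergartens are randomised, and section {16a} describes no stratification on baseline scores. Stable differences between children and between kindergartens therefore stay in the error term for all eight domains (five SDQ, three EmQue). The same raters will already have measured those differences on the same instrument before allocation. At stake is the precision of the domain-level results, which readers will use to judge where the programme works.

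**Working it through.** **Is the model really one wave?** SDQ: 25 teacher + 25 parent = 50. EmQue: 19 + 19 = 38. Each total is two raters at one time point. A model that also measured the domains at T1 would have 100 and 76 indicators. The counts rule out T1 indicators; they do not by themselves rule out a T1 covariate. The latent change score analysis later in {20b} concerns how SDQ and EmQue scores influence each other, not the arm effect on subscales, so it does not supply the baseline.

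**Inputs from Sample size {14}.** 30 kindergartens per arm, mean size m = 15, 900 children, SD 1, ICC 0.065, coefficient of variation of cluster size 0.65, two-sided alpha 0.05, power 0.80, detectable difference 0.27. The same section gives SDQ domain ICCs of 0.015 to 0.064.

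**Reproducing the plan's figure (post-only, no baseline credit).**

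- λ = m·ICC / [1 + (m − 1)·ICC] = 0.975 / 1.91 = 0.510
- Relative efficiency = 1 − 0.65² × λ(1 − λ) = 0.894
- Design effect = 1.91 / 0.894 = 2.136
- SE = √(4 × 2.136 / 900) = 0.0974
- Detectable difference = (1.960 + 0.842) × 0.0974 = 0.273; power at 0.27 = 0.79

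This agrees with the stated 0.27 at 80%. The plan's figure is itself a post-only calculation, so it is a fair benchmark for a post-only subscale contrast with the same inputs.

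**Same steps at ICC 0.015.** λ = 0.225 / 1.21 = 0.186; relative efficiency 0.936; design effect 1.293; SE = √(4 × 1.293 / 900) = 0.0758; power at 0.27 = 0.945.

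**Adding the T1 domain score.** If the baseline-to-post correlation is r at both levels, the SE is multiplied by √(1 − r²). The documents do not give r; 0.3 to 0.7 is an assumption.

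| r | SE factor | SE, ICC 0.065 | Power at 0.27, ICC 0.065 | Power at 0.27, ICC 0.015 |
|---|---|---|---|---|
| post-only | 1.000 | 0.0974 | 0.79 | 0.945 |
| 0.3 | 0.954 | 0.0929 | 0.83 | 0.962 |
| 0.4 | 0.917 | 0.0893 | 0.86 | 0.973 |
| 0.5 | 0.866 | 0.0844 | 0.89 | 0.984 |
| 0.6 | 0.800 | 0.0779 | 0.93 | 0.994 |
| 0.7 | 0.714 | 0.0696 | 0.97 | 0.999 |

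At d = 0.219, the pooled mean cited in {14}, power at ICC 0.065 rises from 0.61 to 0.65 (r = 0.3), 0.74 (r = 0.5) and 0.88 (r = 0.7).

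**Correlation only within kindergartens.** Take r = 0.5 within and 0 between, at ICC 0.065. The variance of a kindergarten mean goes from 0.065 + 0.935/15 = 0.1273 to 0.065 + 0.75 × 0.935/15 = 0.1118. The ratio is 0.878 and power at 0.27 is 0.84 instead of 0.89.

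**The case against.** The strongest reply is that the text is being read too hard. The wave and the item counts describe the measurement part of the model. Treatment arm is not in the count either, yet it must enter somewhere. A covariate list for an additional analysis could sit in a fuller plan that is not shown. This stands in part: the wording does not strictly exclude a T1 covariate. But section {20b} goes into enough detail to name wave, indicators, parcelling and estimators, and the model it describes is post-only.

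Three stronger readings are tempting, and the documents do not support them.

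- **That the subscale estimates would be biased.** They would not. Arms are randomised, and chance baseline imbalance is part of the sampling error that the standard error already covers.
- **That the total-score and subscale analyses answer different questions because only one uses the baseline.** In a linear model, the adjusted and unadjusted T2 contrasts target the same mean difference. The analyses do differ, in a trajectory of a total score against latent domains at one wave, but a T1 covariate does not change that and does not make one model match the other.
- **That the subscale analysis falls short of the planned power.** Post-only power of 0.79 is in line with the planned 80%, because the sample size takes no credit for baseline. The loss is relative to a better model that is available.

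It also stands that ICC 0.065 is the least favourable case. At ICC 0.015, post-only power is already about 0.945 and the possible gain is at most about 5 points. Finally, the arithmetic is for observed scores with SD 1. It approximates the latent model and was not derived for ordinal items under WLSMV.

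**Conclusion.** The point holds as one of precision. As written, the subscale effectiveness analysis uses one post-intervention wave and names no baseline term, although suitable pre-allocation data will be in hand. On the assumed range of r, adjustment lowers the standard error by about 5% to 29%. At d = 0.27 that is worth roughly 4 to 18 points of power at ICC 0.065 and 2 to 5 points at ICC 0.015. It is worth less if kindergarten-level correlation is weak. The direction does not depend on the exact r, provided that it is materially above zero and the baseline enters as a covariate; the size does.

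These are additional analyses. The primary and secondary total-score conclusions are unaffected, and a reader should not infer that the trial as a whole ignores its baseline. The change is worth making because it is nearly free and, with recruitment not yet begun according to Trial status, can be fixed before any data are seen.

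**What to change.** In section {20b}, state that each post-intervention latent SDQ and EmQue domain is regressed on arm plus the T1 score for the same domain, in both the item-level and the parcel model. Since CT-C(M-1) anchors the trait on a reference rater, say how the raters map. Either the reference rater's T1 score predicts the trait factor and the other rater's T1 score predicts the corresponding method factor, or both raters' T1 domain scores enter as covariates. Report the subscale effects as baseline-adjusted.

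The cost is a sentence or two of text, a few more parameters in each Mplus model, and a stated rule for the rare missing T1 score. No new data are needed.
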